### Data storage

The data will be stored in Amazon Relational Database Service (RDS) for PostgreSQL, an open-source object-relational database. Amazon RDS makes it easy to set up, operate, and scale PostgreSQL deployments in the cloud. The automated backup feature of Amazon RDS enables recovery of the PostgreSQL database instance to any point in time within the specified retention period up to thirty-five days. The data is secured through a security layer (access, authorizations, cybersecurity, etc.), applied over the pseudonymization approach.

### Statistical analyses

Descriptive statistics will be generated for all clinical characteristics and outcome measures as appropriate.

In FAITH, variables will be selected using algorithms based on different feature selection methods. For example, for wrapper methods, we will use forward selection, backward elimination, and stepwise selection. These methods can also support filtering, as they evaluate possible combinations of features against the evaluation criterion [50]. The evaluation criterion depends on the type of problem e.g. for regression, evaluation criteria can be *p*-values, R-squared, Adjusted R-squared. Similarly, for classification, the evaluation criteria can be accuracy, which in this case will work as filtering. These methods will help towards eliminating unnecessary variables, or substitute variables with others that will yield a similar prediction [50].

This step of variable selection is fundamental to determine the set of variables that will provide the best fit for generating a model. The correct interaction of variables will support the identification of correlations and interplays among clinical, sociodemographic, psychographic and depression markers, gaining deeper insights for more effective models.

Pre-selected statistical tools according to suitability to support modelling of the selected markers as predictors of depression comprise temporal data mining, time-series analysis, sequence classification methods, clustering of time series, temporal pattern discovery and association rules. If any of these techniques is found not to be suitable, a similar alternative technique will be explored. Because the FAITH data is non-stationary, time series forecasting and neural network analysis modelling will be used to predict future values, for example of presence and severity of depression, based on observed and data of the pre-selected markers. Thus, this statistical methodology will support forecasting by creating a predictive model for risk of depression, anxiety, and quality of life. Additionally, there are several time-series forecasting algorithms that may be useful for this analysis, among which Autoregressive and Moving Average to predict future values as a combination (e.g., linear combination) of values obtained from the sample.

While missing data could introduce bias, and potentially even invalidate results and conclusions, excluding participants with missing data could affect the power of analysis. The strategy of the FAITH project to handle missing data within its prospective datasets will be at first to identify a model for the missing data, which can be based on its distribution conditioned by the available data, as well as to detect if it can be categorized by whether the missing data is random or not. Secondly, missing data patterns will be checked as to detect if only one variable is missing (univariate) or more than one variable (multivariate, monotone, and non-monotone). According to this analysis, the most suitable method to address missing values will be selected among the following: replacing missing values with mean of observed values, omitting participants with missing values (complete case analysis), missing indicator method (creating dummy variable, e.g., zero as an indicator for missing data), mean substitution (replacing missing value with overall mean or subgroup mean). More complex methods may also be considered, such as maximum likelihood method or multiple imputation.

Although FL is a central component of this project, it is important to clarify that it will only be implemented after the trial is concluded (beta version), and not throughout its duration (alpha version). Likewise, an appropriate FL model can only be developed once the data is analysed.

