## Background

There were an estimated 3.9 million new cases of cancer in Europe in 2018 [1]. Due to advances in cancer screening and early diagnosis, cancer survival rates have increased substantially over the past decades, with approximately half of patients diagnosed with cancer expected to survive for 10 years or more [2]. Cancer survivors may face different physical and/or psychosocial sequelae caused by the illness or the treatments. Frequently, these patients report symptoms such as pain, fatigue, cognitive impairment, sexual dysfunction, sleep disturbances, distress, anxiety, or depression [3–5].

Both depression and anxiety are common symptoms among cancer patients, with higher prevalence rates compared to the general population [6]. Noteworthy, the proportion of subjects with anxiety/depression is higher among cancer survivors up to 5 years since cancer diagnosis [7], although such symptoms are often unnoticed or are dismissed as general symptoms of cancer [4, 8]. Among long‐term cancer survivors, a recent review [3] estimated that the pooled prevalence of patients with depressive symptoms was 21%. Until depression is eventually diagnosed and treated, these patients have gone through substantial suffering and experienced greatly reduced quality of life. Individuals with unaddressed and/or untreated depression are more likely to experience exacerbation of symptom burden and are less likely to exercise, present worse quality of life, greater psychological burden on the family, and increased health care utilization and expenditures [9–11]. Also, depression may be related to increased suicidality [6]. The early identification of depressive symptoms is thus of critical relevance.

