## Methods

### Outcomes

The primary outcome will be severity of depressive symptoms as measured by the Hamilton Depression Rating Scale (Ham-D_17_), a semi-structured interview, at months 3, 6, 9 and 12 post-baseline. Secondary outcomes include self-reported anxiety and distress according to the HADS scale, and perceived quality of life measured by EORTC questionnaires at baseline and monthly until month 12.

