#### Sample size

Recruitment will be based on the calculation of sample size, performed with a set of multiple linear regressions, calculated using three inputs: the expected effect size, the chosen significance level (between 0.5 – 0.10), and power (0.8 – 0.95). Based on these, we propose the following sample plan:

An estimation to have a sample size of *n* = 231 (300 subjects, considering an estimated attrition rate of 23%) is sufficient to ensure 85% power at *p* < 0.05 for detecting the cumulative contribution of up to 27 independent predictors (from our group of variables collected from the 4 modules). Furthermore, in a regression model with 27 independent variables this sample size is sufficient to detect the significant added value of each individual independent variable assuming a small effect size (Cohen’s f2 > 0.039).

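### Accuracy is the only criterion named for selecting classification features; with cases a probable minority, it would drop most weak to moderate markers

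*Protocol article*

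**What the plan says.** The Statistical analyses section describes wrapper methods for variable selection and says that the evaluation criterion depends on the type of problem. For regression it lists three examples: p-values, R-squared and adjusted R-squared. For classification it lists one: "for classification, the evaluation criteria can be accuracy, which in this case will work as filtering". The purpose is then stated: "These methods will help towards eliminating unnecessary variables, or substitute variables with others that will yield a similar prediction". The same section foresees a binary target, since future values are to be predicted "for example of presence and severity of depression".

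The only figure in the article for how common cases might be is in the Background, where a review of long-term survivors "estimated that the pooled prevalence of patients with depressive symptoms was 21" per cent. The Exclusion criteria remove people with a current moderate to severe major depressive episode at baseline. The article gives no expected case share for this cohort and no case threshold on Ham-D or HADS.

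Under Outcomes, the primary outcome is on a severity scale: "The primary outcome will be severity of depressive symptoms as measured by the Hamilton Depression Rating Scale". The classification branch is therefore not the primary outcome scale.

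**The concern.** The Background and Discussion present the product as a tool for early screening and advance warning, where missed cases are the costly error. Accuracy counts all correct calls alike. When most people are non-cases, it is dominated by correct negative calls. With the usual 0.5 cut-off, accuracy rises only when a marker moves some predicted risks above one half. A marker that separates low from moderate risk is informative, yet it leaves accuracy almost where it was. A selection step driven by accuracy would then treat it as unnecessary and remove it.

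At stake is the content of any classification model: nutrition, sleep, activity or voice markers of modest strength could be discarded before the model is built. The Sample size section plans for a small effect of each individual predictor, so modest markers are the kind that the study expects.

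**Working it through.** **Inputs from the protocol article.** Analysable sample 231, 300 recruited, 23% attrition, 27 predictors, f² = 0.039, 85% power (Sample size); cited prevalence 21% (Background).

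**Assumptions, not in the article.** Separation d between cases and non-cases of 0.3 to 1.2 standard deviations; case shares other than 21%; a 0.5 cut-off; unweighted classes; one normally distributed marker with equal variance in both groups.

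**1. The plan's own figure.** The article gives "231 (300 subjects, considering an estimated attrition rate of 23" per cent: 231 / (1 − 0.23) = 300. An F test for one predictor among 27 with f² = 0.039, 1 and 231 − 27 − 1 = 203 degrees of freedom and noncentrality 0.039 × 231 has 84.8% power. The statement that the sample "is sufficient to ensure 85% power at" the 5% level is reproduced for a single predictor. It concerns linear regression and says nothing about classification.

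**2. The rule that flags nobody.** Accuracy = 1 − 0.21 = 79%, sensitivity 0. Missed cases: 0.21 × 231 = 48.5, about 49. At a 10% case share the same rule scores 90%.

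**3. Best accuracy that one marker can reach.** With case share p, the best cut is c = d/2 + ln((1 − p)/p)/d, and accuracy = p(1 − Φ(c − d)) + (1 − p)Φ(c). AUC = Φ(d/√2).

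For p = 0.21 and d = 0.5: c = 0.25 + 1.325/0.5 = 2.90, so accuracy = 0.21 × 0.008 + 0.79 × 0.998 = 79.02%. The gain is 0.02 points, or 0.06 of a participant in 231.

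- d = 0.8 (AUC 0.71): 79.6%, gain 0.6 points (about 1.4 participants), sensitivity 10%.
- d = 1.0 (AUC 0.76): 80.6%, gain 1.6 points, sensitivity 20%.
- Four independent markers of d = 0.5 taken together (joint AUC 0.76): gain 1.6 points.
- d = 0.5 at other case shares: gain 0.4 points at 30% and 9.9 points at 50%.

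**4. A binary illustration (assumed figures).** A marker present in 30% of people carries a risk of 40%, against 13% without it. Prevalence = 0.3 × 0.40 + 0.7 × 0.13 = 21.1%, so flagging nobody scores 78.9%. Flagging on the marker scores 0.3 × 0.40 + 0.7 × 0.87 = 72.9%. Accuracy falls, although the marker has a risk ratio of 0.40/0.13 = 3.1, sensitivity 0.12/0.211 = 0.57, specificity 0.609/0.789 = 0.77 and AUC 0.67.

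**5. Simulation of selection at n = 231 (500 runs per row).** A marker is kept by accuracy if 10-fold cross-validated logistic accuracy beats the majority rule; by the AUC test if a rank test gives p < 0.05; by log-likelihood if cross-validated log-likelihood improves on the intercept alone.

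| Case share | d | Accuracy | AUC test | Log-likelihood |
|---|---|---|---|---|
| 10% | 0.5 | 3% | 56% | 77% |
| 10% | 0.8 | 12% | 92% | 97% |
| 10% | 1.0 | 25% | 99% | 100% |
| 21% | 0 (noise) | 0% | 4% | 14% |
| 21% | 0.5 | 16% | 85% | 94% |
| 21% | 0.8 | 49% | 100% | 100% |
| 21% | 1.0 | 74% | 100% | 100% |
| 30% | 0.5 | 38% | 93% | 97% |
| 30% | 0.8 | 80% | 100% | 100% |
| 50% | 0.5 | 97% | 96% | 98% |

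The simulation error on 16% is √(0.16 × 0.84 / 500) = 1.6 points. A separate run at 21% gave about 17% (accuracy) and 88% (AUC test) for d = 0.5, about 75% by accuracy for d = 1.0, and about 16% of noise markers kept by log-likelihood.

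**The case against.** The strongest reply is that the article does not commit to accuracy. It is offered as an example of what the criterion can be, techniques may be replaced if unsuitable, and the tuning metric, cut-off and handling of imbalance are details that a full protocol or SAP may settle. This stands as a limit on the wording: a reader might infer that features will be filtered by accuracy, and the text does not say so. But accuracy is the only classification criterion the article names, so the example itself is open to criticism.

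Second, a reader might infer that at most one in five participants will be a case. The article does not support that ceiling. The 21% comes from a cited review; the same Background reports a higher proportion with anxiety or depression up to five years since diagnosis; milder symptoms may enter the study; and with repeated assessments over 12 months the share ever positive could exceed 21%, depending on a threshold that is not stated. A clear minority is probable, no more.

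Third, wrapper methods judge combinations, and markers can jointly move people across a cut-off. That is true, but in step 3 four moderate markers together gain only 1.6 points at 21%.

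Fourth, log-likelihood has its own cost: without a margin it kept 14% of pure-noise markers at a 21% case share and about 20% at 10% and 30%, where accuracy kept 0 to 1%. This stands and shapes the fix. It does not explain the gap, because the AUC test kept noise only about 5% of the time and still kept far more true markers.

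**Conclusion.** The point holds for the classification branch. At the cited 21%, and with a 0.5 cut-off, selection by accuracy at n = 231 would keep a d = 0.5 marker in about 16–17% of runs, against about 85–88% by an AUC test, and would lose about half of d = 0.8 markers. The size depends on the assumed marker strengths, cut-off and case share. It is worse at 10%, smaller at 30% and gone near 50%.

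Three stronger readings are not supported. Accuracy would not discard every predictive marker: at 21% a marker of d = 1.0 is kept in about three runs in four. The primary outcome is not compromised: Ham-D17 severity is continuous, and the criteria listed for regression are different ones. Nor does the article say that accuracy will be the reported measure of performance; it appears only as a selection criterion. The number of cases per candidate predictor is a separate question about overfitting and is not part of this point.

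**What to change.** In the Statistical analyses section, replace accuracy as the classification selection criterion by one of these:

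- cross-validated log-loss or Brier score, with a minimum-improvement or one-standard-error rule so that noise markers are not kept too readily; or
- cross-validated AUC.

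State also that classification models will be reported with AUC, calibration, and sensitivity at a pre-set specificity.

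The cost is about one sentence in the protocol or SAP and no new data. The downsides are that slightly more noise markers may be kept than under accuracy, and that the resulting figures will look less flattering than an accuracy near 80%.

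### The missing-data menu lists mean substitution twice and leaves maximum likelihood and multiple imputation as optional extras, although the primary outcome is a repeated measure with 23% attrition expected

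*Protocol article*

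**What the plan says.** The missing-data paragraph of the Statistical analyses section opens with a warning: "While missing data could introduce bias, and potentially even invalidate results and conclusions, excluding participants with missing data could affect the power of analysis". The first step is to model the missingness from the available data and "to detect if it can be categorized by whether the missing data is random or not". The second is to classify the pattern as univariate or multivariate, monotone or not. The method then follows: "According to this analysis, the most suitable method to address missing values will be selected among the following". The list is "replacing missing values with mean of observed values, omitting participants with missing values (complete case analysis), missing indicator method" and, as a fourth entry, "mean substitution (replacing missing value with overall mean or subgroup mean". The first and fourth entries are the same technique. Outside the list stands one sentence: "More complex methods may also be considered, such as maximum likelihood method or multiple imputation".

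Three other parts of the article set the context:
- Outcomes: the primary outcome is Ham-D at months 3, 6, 9 and 12, with HADS and EORTC scores monthly.
- Statistical analyses: p-values may serve as a criterion for selecting variables.
- Sample size: "300 subjects, considering an estimated attrition rate of 23" per cent leaves 231 for analysis, with 85% power at p < 0.05 and a claim to detect each single predictor at Cohen's f² above 0.039.

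**The concern.** The menu is a stated choice, not a detail left open for an analysis plan, and an analysis plan that follows it inherits it. None of the listed methods uses a participant's own other visits, which are the best information on a missed Ham-D. The only methods named that can do so are optional.

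The results also feed inference. Markers may be kept or dropped by p-value, and the sample size rests on tests of single predictors. Attenuated or confounded slopes can therefore drop real markers or keep null ones, and a mean Ham-D score can carry an interval that is too short.

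The selection step does not protect against this. Observed data can reject missing completely at random (MCAR), but they cannot distinguish missing at random (MAR) from missing not at random (MNAR). The step therefore cannot justify one method over another, and it sets the method after the data have been seen.

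**Working it through.** **Inputs from the article.** 300 recruited, 231 analysable, 23% attrition, 27 predictors, f² = 0.039, alpha 0.05, four Ham-D visits and 12 monthly app assessments after baseline.

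**Assumptions, not in the article.** The attrition rate is used as the missing fraction, m = 0.23. Simulations use N = 300 and standardised variables. Correlations, effect sizes and dropout models are assumed as shown.

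**1. The plan's own figure.** 231/(1 − 0.23) = 300. For one coefficient among 27 predictors (noncentral F, df 1 and n − 28, noncentrality f² × n), power at n = 231 is 84.8%, and 85% needs n = 233. The stated figure is reproduced.

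**2. Mean substitution, interval for a mean, MCAR.** Filling in a constant reduces the variance to (1 − m)σ², and the sum is then divided by N instead of N(1 − m). Reported SE = σ√(1 − m)/√N; true SE = σ/√(N(1 − m)). The ratio is 1 − m = 0.77. Coverage = 2Φ(1.96 × 0.77) − 1 = 87%.

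**3. Mean substitution of the outcome, slope, MCAR.** The filled-in cases contribute no covariance, so the slope becomes (1 − m)β = 0.77β. Coverage depends on the true slope (simulated, one predictor, outcome SD 1):

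| True slope | Coverage of nominal 95% interval |
|---|---|
| 0 | about 95% |
| 0.2 | 84% |
| 0.3 | 71% |
| 0.5 | 29% |

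Check at 0.2: the bias is 0.23 × 0.2 = 0.046 and the reported SE is about √0.77/√300 = 0.051. The shift is 0.9 SE, and Φ(1.96 − 0.9) is about 0.86, close to the simulated value. The loss comes mainly from attenuation, so a null slope keeps its coverage.

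**4. Dropout that depends on earlier symptoms.** Assume that earlier HADS correlates 0.6 with Ham-D and raises dropout.
- Log-odds 0.8 per SD: the mean is 0.10 SD too low, and the mean-substituted interval covers about 49%.
- Log-odds 1.0 per SD: the mean is 0.12 SD too low. Coverage is 36% with mean substitution (reported SE 0.049, true 0.064) and 54% with complete case, which has the same bias.

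**5. Missing indicator.** A confounder is 23% missing and the marker's true effect is zero. The false-positive rate runs from about 7% (marker–confounder correlation 0.3, confounder effect 0.3) to about 35% (0.6 and 0.5, MCAR, outcome SD 1). At the upper setting with residual SD 1 it is about 28%.

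**6. Complete case.** Coefficients are unbiased when a predictor is MCAR or its missingness depends only on modelled predictors. The SE is correct but wider (0.077 against 0.067 with full data in the two-predictor simulation). The cost is power. Assume that gaps are independent and take the place of the 23% attrition:

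| Assumed gaps | Complete of 300 | Power, one predictor |
|---|---|---|
| 2% of 16 contacts, any gap excludes | 300 × 0.98¹⁶ = 217 | 82% |
| 5% of 16 contacts, any gap excludes | 300 × 0.95¹⁶ = 132 | 61% |
| 5% of the four Ham-D visits only | 300 × 0.95⁴ = 244 | 87% |

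**7. Comparison.** In the two-predictor simulation (true slopes 0.5 and 0.3, predictor correlation 0.5), multiple imputation of the missing predictor returned 0.50 and 0.30 with 95% to 96% coverage, under MCAR and MAR. For the fully observed predictor (true slope 0.30), mean substitution of the other one gave 0.37 (MCAR, coverage 82%) and 0.40 (MAR, 67%). The missing indicator gave 0.37 under both (82% to 83%).

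**The case against.** The plan is not careless. It examines missingness before choosing, names maximum likelihood and multiple imputation, imposes no simple method, and, under Study design, sends automated alerts about missing data. The randomness check may mean no more than testing for MCAR, which is feasible. The main aim is prediction, where simple filling or an indicator can be workable.

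Much of this stands as mitigation. It does not remove the defect, because the methods suited to repeated outcomes remain outside the list, and p-values and tests of single predictors go beyond pure prediction.

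A reader might also infer more than the article supports:
- **That every listed option fails.** Complete case does not fail under MCAR or predictor-only missingness. Its weaknesses are lost power and biased outcome means when dropout follows symptoms. The article itself concedes the first: "excluding participants with missing data could affect the power of analysis".
- **That the whole menu gives intervals that are too narrow.** That fault belongs to mean substitution. Complete case widens intervals, and the indicator's fault is biased coefficients.
- **That non-wear days will be filled with zero.** The zero in the text is an example code for the missingness dummy. The paragraph does not say how non-wear days are handled.
- **That Ham-D will be understated.** This needs dropout to be more likely among the more depressed, which is plausible but not documented.

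**Conclusion.** The point holds in this form: the menu makes mean substitution a standard option twice over and leaves the methods suited to a repeated outcome optional. Two results rest only on treating 23% as the fraction missing completely at random: slopes fall to 0.77 of their value, and coverage of a mean is about 87%. The other sizes depend on assumptions and should be read as ranges:
- slope coverage from about 95% down to 29% as the true slope rises from 0 to 0.5;
- indicator false positives from about 7% to 35%;
- complete-case power from 61% to 87%, according to how many gaps occur and which of them exclude a participant.

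Under symptom-dependent dropout, the 0.10 to 0.12 SD understatement rests on the assumed correlation and log-odds.

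**What to change.** In the Statistical analyses section and any analysis plan:
1. Delete both mean-substitution options.
2. Make a likelihood-based mixed model using all available visits the primary method for Ham-D, HADS and EORTC scores.
3. Use multiple imputation for missing predictors in the regression models, with monthly HADS as an auxiliary variable.
4. Keep complete case only as a sensitivity analysis, and do not use dummy coding where coefficients are interpreted or tested.
5. Replace the step that tries to detect randomness with an MNAR sensitivity analysis, for example delta-adjusted.

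How imputation is combined with the machine-learning models, and whether non-wear becomes a candidate marker, can be left to the analysis plan. The cost is revised wording and modest extra programming. No new data are needed.
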